### Statistical Analyses

All analyses are based on the intention-to-treat (ITT) principle, including all randomly enrolled subjects. Compared to the control group, if the GTN group did not have an increase in the incidence of adverse reactions and there was no difference in 90-day prognosis between the two groups, we would move forward with a phase 2 trial.

Categorical variables including the proportion of good functional outcomes and the frequency of adverse events will be presented as counts and percentages. χ^2^ test, Fisher exact test, or continuity correction will be used where appropriate for comparison between the two groups. If the continuous variables including NIHSS score and infarct volume conform to the normal distribution, results shall be indicated by mean ± standard deviation and tested by *t*-test, and if they do not conform to the normal distribution, results shall be indicated by median and interquartile range and tested by Mann–Whitney *U*-test. p < 0.05 will be considered statistically significant. SPSS 22.0 software (IBM Inc., Armonk, NY) will be used for statistical analysis.

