### Outcomes

#### Primary Outcomes (Safety Assessment)

The primary safety outcome is SBP <110 mmHg. The primary outcome SBP <110 mmHg was defined as average SBP <110 mmHg within 24 h after GTN has been started. BP will be measured every 15 min between 0 and 2 h after GTN is started, every 30 min between 2 and 12 h, every 120 min between 12 and 48 h, and twice a day after 48 h. The target levels of BP poststroke remain unclear within the available literature (34–37). The current AIS guidelines differentiate BP targets based on a variety of factors including whether the patient receives alteplase, undergoes mechanical embolectomy, and/or experiences a hemorrhagic conversion. Prior studies (34–37) found a U-shaped relation of BP with functional outcome: both low BP and high BP were associated with poor outcome. There is no clearly defined cutoff for low BP in patients with AIS. Previously identified nadirs such as the tipping point in the U-shaped association between BP and outcome also vary between 120 and 180 mmHg (34, 36). Because of this variability, according to prior studies, we will use the lowest 10th percentile as a cutoff, low SBP, namely, SBP <110 mmHg.

The secondary safety outcomes are headache. Headaches related to GTN were defined as follows: GTN responders are those who develop a mild to moderate headache (headache scores 3–6) within 5–15 min with a short-lasting duration (maximum of 30 min) and spontaneously recover within 1 h after administration of GTN without the need for any rescue medication (38). In addition, severe headaches (scores 7–10) or the use of analgesia for GTN-caused headaches will be accounted for as secondary safety outcomes. If patients experience severe headaches, vital signs (i.e., BP, heart rate, body temperature, respiratory rate of the patients) will be closely monitored, and a CT scan will be obtained to analyze the cause of the headache.

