### Estimation of Sample Size

There are no data available for reference because no completed clinical study of intravenous GTN in AIS patients currently exists. However, Hertzog (39) has suggested that 10–20 patients in each group are sufficient to assess the feasibility of a pilot study, while Dobkin (40) has shown that 15 patients in each group is usually enough to decide whether a larger multicenter trial should be conducted. In order to determine the sample size for each group, a power analysis was conducted based on the work of a prior study (20) that GTN can make a difference of 10 mmHg in SBP as compared to placebo groups. For the difference in BP at 10 mmHg, standard deviation at 10 mmHg, in order to have alpha exceed 95%, and beta = 0.8, a sample size of 16 patients per group has been calculated. As we expect to include around 20% for treatment dropouts and crossovers and for losses to follow-up, we will increase this sample size with 20% and aim to recruit 40 patients. The results of this study should be able to determine the initial safety and feasibility of intravenous infusion of GTN in AIS patients. The data will be used to estimate sample size and conduct a power calculation to plan a phase 2 trial for efficacy.

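### Intention-to-treat is set for every analysis, including primary safety, although crossovers and treatment dropouts are expected; this dilutes harm and eases the go rule

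*Protocol article*

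**What the plan says.** Under Statistical Analyses the article sets one population for everything: "All analyses are based on the intention-to-treat (ITT) principle, including all randomly enrolled subjects". No safety set or as-treated analysis is named.

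Under Primary Outcomes (Safety Assessment), "The primary safety outcome is SBP <110 mmHg", defined as "average SBP <110 mmHg within 24 h after GTN has been started". Headache is the secondary safety outcome.

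Under Estimation of Sample Size the planned number is raised to cover "around 20% for treatment dropouts and crossovers and for losses to follow-up". This is one pooled figure. It names crossovers, but does not divide the total between the three causes.

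The Statistical Analyses section also gives the rule for going on to phase 2. Its safety part is met "if the GTN group did not have an increase in the incidence of adverse reactions" relative to control. Its outcome part reads "there was no difference in 90-day prognosis between the two groups, we would move forward with a phase 2 trial".

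**The concern.** ITT is the cautious choice when a trial must show a difference, because departures from allocation pull the arms together. Here the favourable safety result is the absence of a difference, so the same pull works the other way. A GTN-arm patient who never receives GTN is counted as exposed, and a control patient given GTN carries any GTN-caused hypotension or headache into the control arm. If the drug does harm, both make the arms look more alike and a decision to proceed more likely.

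The ITT rule also sits awkwardly with the primary outcome, whose 24 h window runs from the start of GTN. A GTN-arm patient who never starts has no such window, yet must be included.

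**Working it through.** **The plan's own figure.** Inputs from Estimation of Sample Size: difference 10 mmHg, SD 10 mmHg, alpha 0.05 and power 0.80 as usually read, taken as two-sided.

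- n per group = 2 × (1.96 + 0.84)² × 10² / 10² = 15.7, rounded up to 16.
- With 20% added: 16 / 0.8 = 20, or 16 × 1.2 = 19.2, rounded up to 20. Both give 40 in total.

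The stated 16 and 40 reproduce. The calculations below use 20 per arm.

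**Dilution factor.** Let pT and pC be the true risks on GTN and on saline, q the share of the GTN arm not given GTN, and c the share of controls given GTN. Assume that risk depends only on the treatment received.

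- ITT risk, GTN arm = (1 - q) pT + q pC
- ITT risk, control arm = (1 - c) pC + c pT
- ITT risk difference = (1 - q - c)(pT - pC)

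**Illustration.** The documents give no event rates and no values for q or c. Assume pT = 30% and pC = 5%. Worked examples:

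- q = 20%, c = 0: 0.8 × 30% + 0.2 × 5% = 25%, against 5%.
- q = c = 20%: 25%, against 0.8 × 5% + 0.2 × 30% = 10%.

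Power is for a significant excess on GTN (two-sided Fisher exact test at 0.05), by exact enumeration. The last column is the probability that GTN-arm events do not exceed control-arm events.

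| Departure from allocation | ITT risks | Risk difference (points) | Power | Chance of observing no increase |
|---|---|---|---|---|
| None | 30% v 5% | 25 | 45% | 2% |
| q = 5% | 28.75% v 5% | 23.75 | 41% | 3% |
| q = 10% | 27.5% v 5% | 22.5 | 37% | 3% |
| q = c = 5% | 28.75% v 6.25% | 22.5 | 35% | 4% |
| q = c = 10% | 27.5% v 7.5% | 20 | 27% | 6% |
| q = 20% (extreme) | 25% v 5% | 20 | 30% | 5% |
| q = c = 20% (extreme) | 25% v 10% | 15 | 14% | 14% |

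**Other assumed rates.** The direction is the same.

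- 40% v 10%: power falls from 49% to 34% (q = 20%) or 17% (q = c = 20%).
- 20% v 5%: power falls from 17% to 10% or 6%.

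**What an as-treated safety set would recover** (30% v 5%):

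- 20% never start, in both arms alike: 16 v 16 gives 31%, against 30% under ITT.
- 20% never start, in the GTN arm only: 16 v 20 gives 44%, against 30%.
- 10% cross over each way: regrouping by treatment received gives 20 v 20 again, so 45% against 27%, provided crossover is unrelated to risk.

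**The case against.** The strongest objection concerns size. The 20% is a single allowance, and most of what it covers does not dilute this outcome.

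- Loss before day 90 hardly touches a blood pressure average over the first 24 h.
- A treatment dropout is not the same as a patient who never started. Someone whose infusion is stopped for hypotension or headache is still a GTN-arm event under ITT.
- The GTN headache is defined as arising within 5-15 minutes, so brief exposure captures it.

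Only never-started patients and true crossovers clearly dilute, with some effect of shortened exposure on the 24 h average. A reader might infer that a fifth of each arm dilutes the comparison and that power of 14% is to be expected. The article does not support this: that row turns the whole allowance into two-way crossover and leaves nothing for dropout or loss.

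It is also fair that the remedy excludes never-started patients and so loses numbers. A reader might take 45% as what it would restore in every case, but with equal non-start in both arms it regains almost nothing (31% v 30%).

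Finally, sample size is at least as great a weakness. If no increase means a non-significant test, the rule misses a 30% v 5% harm 55% of the time (1 - 0.45) with perfect compliance.

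These points stand, and they limit the size. They do not reverse the direction, and the rule cannot be put down to condensation: the article states it for all analyses and makes no exception for safety.

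**Conclusion.** The point holds as a matter of direction. ITT as the only basis for the safety comparison shrinks any true excess by (1 - q - c), in a trial whose go rule rewards seeing no excess.

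The size cannot be fixed from the document. Under the assumed 30% v 5% with 20 per arm, departures of 5-10% take power from 45% to between 41% and 27%, and raise the chance of observing no increase from 2% to about 3-6%. The 30% and 14% powers, and the 14% chance of observing no increase, are upper bounds on the damage at these rates, not forecasts. The results rest on the assumed rates, on risk following treatment received, and on never-started patients carrying the control risk, since the article does not say how they would be counted.

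It would go too far to infer that ITT alone makes the go rule unreliable, because the small sample does at least as much. The case for the change is chiefly less bias, with a material power gain only when non-start is confined to the GTN arm or there is true crossover.

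**What to change.** Limit the ITT sentence to efficacy (mRS, NIHSS and infarct volume). Define a safety set of all patients who started a study infusion, analysed by treatment actually received, for SBP <110 mmHg, headache and adverse events. Show the ITT safety table alongside, and say that the safety part of the go decision rests on both. Report never-started patients and crossovers by arm, so that q and c can be read off.

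The cost is a change of wording and one further table; sample size and conduct are unchanged. There are two downsides: the as-treated comparison is not strictly randomised for crossovers, which the paired ITT table helps to check, and leaving out never-started patients costs some numbers.

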## Abstract

**Background:** Despite intravenous thrombolysis and endovascular therapy for acute ischemic stroke (AIS), many survivors still have varying degrees of disability. Glyceryl trinitrate (GTN), a nitric oxide (NO) donor, has been previously reported to induce neuroprotection after AIS. The use of GTN to reduce brain damage after stroke remains yet to be elucidated. This study was designed to explore the safety, feasibility, and preliminary efficacy of intravenous administration of GTN after AIS.

**Methods:** A prospective randomized controlled trial is proposed with AIS patients. Participants will be randomly allocated to GTN group and control group with a 1:1 ratio (*n* = 40). Both groups will be treated with standard therapies according to the current stroke guidelines. Participants allocated to the GTN group will receive intravenous administration of GTN (5 mg GTN in 50 ml saline at a rate of 0.4 mg/h that is continued for 12.5 h/day for 2 days) within 24 h of symptom onset. Participants allocated to the control group will receive intravenous administration at equal capacity of 0.9% normal saline (NS) (total 50 ml/day at 4 ml/h that is continued for 12.5 h/day for 2 days). The primary outcome is safety [systolic blood pressure (SBP) <110 mmHg, headache], while the secondary outcomes include changes in functional outcome and infarction volume.

**Discussion:** Rapid Intravenous Glyceryl Trinitrate in Ischemic Damage (RIGID) is a prospective randomized controlled trial that aims to ascertain the safety, feasibility, and preliminary efficacy of intravenous GTN as a neuroprotection strategy after AIS. These results will provide parameters for future studies as well as provide insights into treatment effects. Any possible neuroprotective qualities of GTN in AIS will also be elucidated.

**Trial Registration:**www.chictr.org.cn, identifier: ChiCTR2100046271.

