## Methods

### Study Design

This study is a phase 1, single-center, prospective RCT. Participants will be patients with AIS within 24 h onset. Patients meeting the inclusion criteria but not the exclusion criteria will be randomly allocated to the GTN group or the control group. Both groups will be treated with the standard management according to the guidelines (30). GTN will be administered by continuous intravenous pump (5 mg GTN in 50 ml saline with a speed of GTN 0.4 mg/h continued for 12.5 h/day for 2 days) within 24 h of symptom onset in the GTN group. The control group will receive intravenous administration of equal capacity of 0.9% normal saline (NS) (total 50 ml/day at 4 ml/h continued for 12.5 h/day for 2 days). The clinical characteristics, medical history (diabetes, hypertension, hyperlipidemia, coronary heart disease, stroke, atrial fibrillation), smoking history, alcohol drinking history, and National Institutes of Health Stroke Scale (NIHSS) score at admission will be collected. Magnetic resonance imaging (MRI) will be performed at baseline and on day 7 ± 1. NIHSS and modified Rankin Scale (mRS) will be assessed at baseline and on days 1, 7, 14, 30, and 90.

All participants or proxies will be informed of potential risks and possible benefits and consent to this study. This consent will be provided to a legal representative if the patients do not have the capacity to consent. This study was approved by the ethics committee of Luhe Hospital, Capital Medical University, Beijing, China, and has been registered at www.chictr.org.cn with ChiCTR2100046271. An independent physician will monitor the health and safety of the participants.

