#### Secondary Outcomes (Efficacy Assessment)

The primary efficacy outcome is the mRS at 90 days (mRS scores of 0–2 indicate functional independence). Secondary efficacy outcomes include the rate of the 0–2 mRS at 90 days, the incidence of death at 90 days, blood nitrate index detection at 1 day [cyclic guanosine monophosphate (cGMP, second messenger to NO), L-arginine (substrate for NO), and L-citrulline (co-product with NO)], infarct volume, as well as NIHSS scores at days 1, 7, 14, 30, and 90. The mRS and NIHSS scores will be obtained by a blinded personnel to the research. Face-to-face encounters in the consultation room will be used in the study to calculate mRS and NIHSS. Brain infarct volume will be determined by MRI diffusion-weighted imaging technique. The lesion profile plotted at each individual level by an image tool [region of interest (ROI)] on the workstation will be used to calculate the area. The levels will be multiplied by the thickness of each level and summed to calculate the infarct volume. The calculations will be performed by personnel blinded to clinical data and randomization at baseline and at day 7 ± 1.

Patients diagnosed as AIS without corresponding lesions on MRI are rare (<2%) in our stroke center. Patients who are misdiagnosed with stroke through negative MRI will be reported, and subgroup analysis will be performed.

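### NIHSS and infarct volume are assigned unadjusted tests chosen by a normality check although baseline values exist, and the 90-day mRS has no test of its own: an avoidable loss of precision

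*Protocol article*

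**What the plan says.** **Tests.** The Statistical Analyses section of the protocol article begins its rule for continuous outcomes with "If the continuous variables including NIHSS score and infarct volume conform to the normal distribution". In that case "results shall be indicated by mean ± standard deviation and tested by" a t-test; otherwise "results shall be indicated by median and interquartile range and tested by" a Mann–Whitney U-test. Proportions, including that of good functional outcomes, go to a chi-square, Fisher or continuity-corrected test. No covariate and no criterion for normality are named.

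**Baseline data.** Study Design states that "NIHSS and modified Rankin Scale (mRS) will be assessed at baseline and on days 1, 7, 14, 30, and 90" and that "Magnetic resonance imaging (MRI) will be performed at baseline and on day 7 ± 1". The Secondary Outcomes section has infarct volume calculated at both MRI times.

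**Scale.** The Abstract says that "the secondary outcomes include changes in functional outcome and infarction volume". The Statistical Analyses section does not say whether NIHSS and infarct volume are compared as final values or as changes.

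**mRS.** The Secondary Outcomes section states: "The primary efficacy outcome is the mRS at 90 days (mRS scores of 0–2 indicate functional independence". It then lists the rate of mRS 0–2 on the same day as a separate secondary efficacy outcome.

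**The concern.** Three features of the stated analysis are weak for a trial with about 20 patients per arm.

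- **Unadjusted tests.** Entry NIHSS may lie anywhere from 3 to 16, so patients differ widely at the start. If baseline severity and lesion size predict the later values, a two-sample test leaves that variation in the error term.
- **A test chosen by the data.** A normality check on some 20 values per arm is a weak guide. It could send NIHSS to a t-test at one visit and to a rank test at another, so that the reported quantity changes within one trial.
- **No named test for the primary efficacy outcome.** The only functional analysis named is the 0–2 proportion, which is the secondary. If that proportion became the working analysis, the information in the ordered scale would be lost. The same section makes progress to phase 2 depend partly on finding no difference in 90-day prognosis, and a low-powered test makes that finding easier to reach.

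**Working it through.** **The plan's own figure.** The sample-size section uses a 10 mmHg difference and an SD of 10 mmHg. I read its error rates as two-sided alpha 0.05 and power 0.80. Then n per arm = 2 × (1.960 + 0.842)² × (10/10)² = 15.7, so 16. Allowing for 20% loss, 32/(1 − 0.20) = 40, or 20 per arm. The stated 16 and 40 reproduce, and nothing below overturns them.

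**Inputs for the adjustment.** The 20 per arm comes from the protocol. The correlation r between the baseline value and the outcome is not in the documents, so I assume 0.3, 0.5 and 0.7. The effect of 0.8 SD is also an assumption, used for illustration.

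**Formulas, with the unadjusted final-value variance set to 1.**
- ANCOVA residual variance: 1 − r²
- Change-score variance, with equal SDs at both times: 2(1 − r)
- Equivalent patients per arm under ANCOVA: 20/(1 − r²)
- Power: two-sided two-sample t-test at 0.05, 20 per arm, with effect 0.8 divided by the square root of the variance. The one degree of freedom spent on the covariate is ignored.
- Detectable difference at 80% power (normal approximation): 2.802 × √(2/20) × √variance

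| r | ANCOVA variance | Equivalent n per arm | Power, final value | Power, ANCOVA | Power, change | Detectable difference, final value | Detectable difference, ANCOVA |
|---|---|---|---|---|---|---|---|
| 0.3 | 0.91 | 20/0.91 = 22.0 | 69% | 73% | 55% | 0.89 SD | 0.85 SD |
| 0.5 | 0.75 | 20/0.75 = 26.7 | 69% | 81% | 69% | 0.89 SD | 0.77 SD |
| 0.7 | 0.51 | 20/0.51 = 39.2 | 69% | 93% | 89% | 0.89 SD | 0.63 SD |

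The change-score column shows why the undefined scale matters. Below r = 0.5 a change score is noisier than the final value alone, since 2(1 − 0.3) = 1.4. In all three rows ANCOVA has the highest power.

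**Chance imbalance.** The standard error of the difference in baseline means is √(2/20) = 0.32 SD. By the normal approximation, an imbalance above 0.3 SD has probability 34%, and one above 0.5 SD has probability 11%.

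**mRS.** The documents give no distribution, so I assume control-arm percentages of 15, 20, 15, 20, 15, 5 and 10 for scores 0 to 6 (50% at 0–2) and a common odds ratio across cut-points. Power from 5,000 simulated trials of 20 per arm:

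| Assumed odds ratio | Mann–Whitney, full scale | Fisher, 0–2 | Uncorrected chi-square, 0–2 |
|---|---|---|---|
| 2 | 22% | 11% | 17% |
| 3 | 47% | 26% | 37% |
| 4 | 67% | 41% | 53% |

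In this example the 0–2 cut loses power with either test. The loss is larger with Fisher's test, which is conservative at this size.

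**The case against.** The strongest reply is that nothing here is an error. Randomisation makes the unadjusted comparison unbiased, and its error rate already allows for chance imbalance. Covariates and model forms are commonly left to an analysis plan, and this is a small phase 1 study with a safety primary outcome and efficacy called preliminary. The first part stands in full: this is not a validity problem. The second stands only in part, because the article does name specific tests, and an analysis plan with adjusted models would have to replace published text.

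A reader might infer three stronger things that the documents do not support.

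- **That only post-treatment values are compared.** The Statistical Analyses section does not say so, and the Abstract speaks of changes. The supportable point is that the scale is undefined.
- **That the mRS is collapsed to 0–2 or never analysed as a scale.** The Secondary Outcomes section lists the mRS and the 0–2 rate separately. The lists of variables in the analysis section are open, so a Mann–Whitney test of the mRS is not excluded. It is simply not assigned.
- **That the same criticism covers systolic pressure.** In the outcomes section this is a binary safety outcome, and no continuous test of it is named. At the plan's own 10 mmHg and SD 10, unadjusted power with 20 per arm would already be 87%.

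It would also go too far to say that the noise necessarily carries into phase 2. The sample-size section says that the data will inform that calculation, but not through which endpoint or SD, and the baseline data will still be there to use.

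**Conclusion.** The point holds as a free improvement in precision. The plan names unadjusted tests selected by a normality check, although baseline NIHSS and infarct volume are available. It does not define the scale of comparison, and it assigns the primary efficacy outcome no test distinct from the mRS 0–2 secondary.

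The gain from adjustment depends on a correlation that the documents do not give. At 0.3 it is slight (about two patients per arm). At 0.5 it is worth about seven, and at 0.7 about nineteen, close to doubling the arm. The mRS figures rest on an assumed distribution and on proportional odds, and they show direction and rough size only. The sample size and the primary safety analysis are unaffected.

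**What to change.** In the Statistical Analyses section:

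1. Analyse NIHSS at each visit and day-7 infarct volume by ANCOVA with the baseline value as covariate. Fix the scale (log or rank) in advance for each outcome and drop the normality pre-test. This also settles whether final values or changes are compared.
2. Assign the 90-day mRS an analysis over its ordered categories: a proportional-odds model adjusted for baseline NIHSS, or a Mann–Whitney test as the simple form. Keep mRS 0–2 as the secondary.
3. Report each comparison as an estimate with a 95% confidence interval.

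The cost is wording only. The covariates are already collected, the planned software can fit these models, and no patient, visit or measurement is added.
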